**STUDY DRUGS**

Storage of Study Drugs

All efforts will be made to store the study drugs in accordance with the manufacturers' recommendations in a secure area.

Compliance with Study Drugs

Only the first dose will be administered as Directly-Observed-Therapy. If the patient vomits, and is re-dosed; this will be recorded in the CRF. This is an effectiveness not an efficacy study.

Concomitant Medication

Throughout the study, investigators may prescribe any concomitant medications or treatments deemed necessary (e.g. antipyretics or anti-emetics) to provide adequate supportive care except for antibiotics with antimalarial activity unless unavoidable (e.g. doxycycline, azithromycin). If these are required the patients will be kept in the study and this will be noted as a protocol deviation.

Antimalarials for recurrent infections (see Rescue treatment) and non-falciparum malaria (if applicable) will be prescribed as described above. Any medication, other than the study medication taken during the study will be recorded in the CRF.

**SAFETY REPORTING**

This trial will be using standard drugs that have either been registered for decades and evaluated extensively. Therefore, the safety aspects of this trial will be limited to close observation while patients are in hospital, treating any intercurrent illnesses or drug-related side effects and recording and reporting only serious adverse events.

Definitions

*Adverse Event (AE)*

In this study, an AE is either a drug-related side effect or a new or exacerbation of a pre-existing symptom, sign or illness (other than malaria).

Serious Adverse Event

*A serious adverse event is an AE that:*

results in death

is life-threatening i.e. the patient was at risk of death at the time of the AE

requires inpatient hospitalisation or prolongation of existing hospitalisation

results in persistent or significant disability/incapacity or

is a congenital anomaly/birth defect

requires acute medical or surgical care to prevent one of the outcomes listed above

Reporting Procedures for Serious Adverse Events

All SAEs will be reported by the site investigator to the Medical Monitor, [name], or his designee, within one day of his or her awareness of the SAE..

The site investigator must also report the SAEs to the local ethics committee in accordance with local requirements.

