*Plasmodium vivax* malaria is notoriously difficult to eliminate, largely because of relapses which are derived from activation of liver hypnozoites. The only effective radical treatments for *P.vivax* infections are 8-aminoquinoline antimalarials, all of which produce oxidant haemolyis. These drugs are potentially dangerous in areas where glucose 6 phosphate dehydrogenase deficiency (G6PD) is common (i.e. most tropical countries). Primaquine is widely recommended, but often not prescribed. The proportion of vivax infections which relapse varies considerably across the tropical world. India has most of the world’s *Plasmodium vivax* malaria (1). There have been few prospective studies of relapse patterns in India (2-5). More recent investigations indicated low relapse rates, which was one reason why India adopted a five day primaquine regimen for radical treatment of vivax malaria over the past half-century (6, 7). But relapse rates can be underestimated if follow-up terminates before relapses emerge. Long latency *P.vivax* was prevalent over Europe, and much of Asia. In the temperate areas relapses usually occurred 7 to 10 months after the initial febrile illness. Further north there was usually no primary illness, and symptoms occurred 7-10 months after sporozoite inoculation. Although generally thought to be confined to temperate regions such as the Koreas, long latency *P.vivax* is likely be much more widespread throughout the tropics. It is certainly also prevalent in Central America, North Africa, the horn of Africa, the middle East, Afghanistan, Central Asia, the Indian sub-continent (3) and China. Clear evidence for long latency in Indian *P.vivax* was documented in the first half of the twentieth century (8), and is supported by more recent studies (3). In order to assess the effectiveness of short course primaquine regimens, and to determine whether long latency *P.vivax* was present around Kolkata, a prospective comparative trial supported by parasite genotyping was conducted with up to 450 days follow-up.

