**OBJECTIVES**

*Primary Objective*

To compare the effectiveness of primaquine 0.25mg base/kg/day given for 5 days versus 14 days together with a standard chloroquine regimen in *P*. vivax malaria.

*Secondary Objectives*

To measure the clinical and parasitological responses with chloroquine alone and two chloroquine –primaquine regimens.

To assess safety and tolerability of the different regimens

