***Procedures***

*Informed Consent*

The subject (or witness if illiterate) or the parent or guardian of a minor must personally sign and date the latest approved version of the informed consent form before any study specific procedures are performed. Written and verbal versions of the participant information and informed consent in the local language will be presented to the participants detailing no less than: the exact nature of the study; the implications and constraints of the protocol; the known side effects and any risks involved in taking part. It will be clearly stated that participation is voluntary and that the participant or guardian is free to withdraw from the study at any time for any reason without prejudice to future care, and with no obligation to give the reason for withdrawal.

Written informed consent will be obtained by means of participant or guardian dated signature or thumb print (if unable to write) and dated signature of the person who presented and obtained the informed consent.

*Screening, Eligibility and Baseline Assessments*

Patients who present at the participating sites will be screened to assess eligibility. Full consent/assent will be obtained before any enrolment procedures are conducted. It will be made clear from the outset that refusal to participate will not jeopardize subsequent antimalarial treatment.

*Demographics and Medical History*

Basic demographic and epidemiological data (e.g. sex, age, address, prior treatment and a full medical history) will be recorded by the study staff.

*Physical Examination and Vital Signs*

Physical examination will be conducted by a qualified investigator. Weight, pulse, blood pressure, respiratory rate, temperature, spleen and liver size will be recorded.

*Drug history*

All prescribed or over-the-counter and traditional medications used within the last 7 days will be recorded. Any drug allergies will be recorded.

*Screening blood & urine tests*

- A parasite count from Giemsa stained thick and thin blood films
- Full blood count or haematocrit
- G6PD spot test

*Randomisation and blinding*

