Subjects who fulfil all the inclusion criteria and have none of the exclusion criteria will be randomised 1:1;1 to one of the three treatment arms. Allocation will be done by drawing the next sequential numbered opaque envelope, which contains the study number of the patient referring to the study treatment. The subjects will be assigned a study arm through a computer-generated randomisation scheduleThis is an open-label study so the blinding of investigators and patients is not applicable. However, the randomisation procedure allows for adequate drug allocation concealment before envelopes are opened. All laboratory investigations will be performed without knowledge of the treatment allocation.

*Blood sampling*

On admission

On study admission, immediately before drug administration, blood will be collected for the following:

- parasite count
- EDTA 2mL whole blood sample for PCR parasite genotyping
- haematocrit

G6PD spot test

*Study drug regimens*

(1) chloroquine (25mg base /kg total) only

(2) chloroquine (25mg base /kg total) followed by primaquine 0.25mg base/kg/ day for five days

(3) chloroquine (25mg base/kg total) followed by primaquine 0.25mg base/kg/ day for 14 days

*For recurrences:*

chloroquine (25mg base /kg total) followed by primaquine 0.25mg base/kg daily for 21 days.

The first dose will be observed but all subsequent antimalarial doses will be taken at home. Each patient will be instructed on the need to complete the full course of treatment.

*Follow up procedures*

Patients will be seen daily until a febrile then weekly for one month and thereafter every one to two months for 15 months. If vivax malaria recurs blood will be taken for parasite genotyping and comparison with the original infection.

*Additional visits*

Patients presenting to the clinic with a fever or other symptoms on unscheduled days will be assessed by the study physician. Their temperature will be recorded and blood smear will be made for any patient with a documented fever (oral or tympanic temperature ≥ 37.5˚C) or a history of fever. Patients will be treated as clinically indicated.

Patients with recurrent parasitaemia

Patients with a recurrent parasitaemia during follow up will have blood taken for the following:

- parasite speciation and count
- haematocrit
- if parasitaemic: EDTA 2mL whole blood sample for PCR parasite genotyping

*Discontinuation/ Withdrawal of Participants from the Study*

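### The safety and tolerability objective conflicts with a safety section that records only serious adverse events, and no post-dose haematocrit is stated for patients who complete treatment without recurrence

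*Protocol*

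**What the plan says.** The secondary objectives include "To assess safety and tolerability of the different regimens" (Protocol, OBJECTIVES; the Synopsis has the same aim). No safety endpoint appears in either endpoint list.

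SAFETY REPORTING argues that the drugs are long registered and much studied, so safety work is "limited to close observation while patients are in hospital", treating intercurrent illness or side effects, and "recording and reporting only serious adverse events". The same section then defines an adverse event broadly enough to include non-serious ones. The paragraph on discontinuation and withdrawal asks for an adverse event assessment and a haematocrit, but only when study treatment stops early.

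On dosing, the Procedures section states: "The first dose will be observed but all subsequent antimalarial doses will be taken at home". STUDY DRUGS repeats that only the first dose is directly observed.

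The Background says of the 8-aminoquinolines, "all of which produce oxidant haemolyis". Haematocrit appears among the screening tests ("Full blood count or haematocrit"), in the admission sample taken before dosing, at recurrent parasitaemia and at premature discontinuation. The statistical section plans summaries and paired or unpaired tests of continuous data, including laboratory parameters.

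**The concern.** The objective asks for a comparison between regimens. The safety section restricts what is recorded, not only what is reported quickly, and ties observation to a setting where most doses are not taken. Primaquine follows chloroquine in both combination arms, so the 5-day and 14-day courses that distinguish those arms are taken at home.

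At stake is the safety side of the choice between 5 and 14 days. If few serious events occur, a report could describe both regimens as well tolerated without systematic data on non-serious events or haemolysis. An analysis plan cannot repair this, because it cannot analyse what was not collected.

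**Working it through.** **1. The plan's own figure.** The only quantitative target is 50 per arm, sized on relapse of 30% against 4%, with 95% confidence (read as two-sided 0.05), 80% power and 20% loss.

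- Pooled-variance formula: n = [1.960·√(2·0.17·0.83) + 0.842·√(0.30·0.70 + 0.04·0.96)]² / 0.26² ≈ 31.6, so 32 per arm.
- With continuity correction: (31.6/4)·[1 + √(1 + 4/(31.6·0.26))]² ≈ 38.9, so 39 per arm.
- Allowing for loss: 39/0.80 = 48.75, so 49, against the stated 50.

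The figure reproduces to within one patient. There is no arithmetic fault, and no part of the sizing concerns safety.

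**2. What is captured, and from whom.**

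| Item | Where stated | Who contributes |
|---|---|---|
| Serious adverse events | SAFETY REPORTING | All arms |
| Adverse event assessment | Discontinuation/Withdrawal | Only patients who stop treatment early, on a best-effort basis |
| Reason for withdrawal | Discontinuation/Withdrawal | Only withdrawn patients |
| Re-dosing after vomiting | STUDY DRUGS, compliance | In text about the observed first dose |
| Non-study medication | STUDY DRUGS, concomitant medication | All arms; an indirect marker |
| Haematocrit | Screening; admission | All, before dosing |
| Haematocrit | Recurrent parasitaemia | Only patients whose malaria recurs |
| Haematocrit | Discontinuation/Withdrawal | Only patients who stop early, on a best-effort basis |

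The admission sample is introduced with "On study admission, immediately before drug administration, blood will be collected for the following", so it is a baseline value. No row gives non-serious adverse events for all randomised patients, and none gives a post-dose haematocrit for a patient who completes treatment without recurrence.

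**3. How selective the recurrence haematocrits would be.** Take the protocol's relapse assumptions, assume that every relapse yields a haematocrit, and ignore loss and discontinuations.

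- Chloroquine only: 0.30 × 50 = 15 with a value, 35 without.
- Primaquine for 14 days: 0.04 × 50 = 2 with a value, 48 without.
- Primaquine for 5 days: no relapse rate is assumed in the protocol. If it lies between 4% and 30%, 2 to 15 would have a value and 35 to 48 would not.

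These values are taken at varying times, during acute malaria, and only in patients selected by the primary outcome, which the regimens are expected to change. They cannot serve as a randomised comparison of haemolysis.

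**4. What the arm size could support.** If a post-dose haematocrit existed in all arms, the standardised difference detectable with 80% power is (1.960 + 0.842)·√(2/n): 0.63 SD with 40 evaluable per arm, 0.56 SD with 50. The trial is not too small for a useful comparison; what is missing is a statement that the measurement is made.

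**The case against.** The strongest reply is that the restriction is deliberate: the drugs are old and their toxicities well described. Patients also have a G6PD spot test, and the main exclusion criteria keep those found deficient out of the primaquine groups. That explains a light safety plan. It does not explain keeping an objective to assess tolerability of the different regimens. The Synopsis, moreover, excludes only severe G6PD deficiency, so the two lists themselves need reconciling.

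Four stronger readings are tempting, and the documents do not support them.

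- A reader might infer that the objective cannot be addressed at all. Serious events, withdrawal reasons, discontinuation assessments, re-dosing after vomiting and concomitant medication are recorded, and symptomatic patients are assessed at unscheduled visits. Discontinuations for adverse events and concomitant medication can be compared between arms. This is limited and selective, but it is not nothing.
- A reader might infer that no haematocrit is taken after dosing. The follow-up paragraph gives visit times only. It also omits routine smears and temperatures, which the clearance-time endpoints need, so it is not an exhaustive list. The planned paired tests are compatible with repeat measurement. What can be said is that the protocol does not state such a value. The restriction to serious adverse events, by contrast, is express text.
- A reader might infer that nobody looks once patients leave hospital. Only the first of the three activities in the safety sentence is tied to hospital, and patients are seen daily until afebrile and then weekly for a month.
- A reader might cite the exact 95% upper limit after zero serious events, 1 − 0.025^(1/50) = 7.1%, or 8.8% with 40 patients, as the size of the fault. The arithmetic is right, but the limit depends only on arm size and would be the same after any change to recording. The 8.8% also applies the relapse calculation's loss allowance to a primaquine course of at most 14 days.

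**Conclusion.** The point holds as a contradiction within the protocol. A secondary objective calls for an assessment of safety and tolerability of the regimens, while the safety section excludes recording of non-serious adverse events and centres observation on hospital although dosing is at home. Followed as written, the protocol yields no systematic tolerability data for a randomised comparison of 5 with 14 days of primaquine. It also states no post-dose haematocrit for patients who complete treatment without recurrence: about 35 of 50 on chloroquine alone and 48 of 50 in the 14-day arm, under the assumptions in step 3 of the working.

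The haematocrit part rests on what the protocol leaves unstated and is therefore weaker than the adverse event part. The point should be fixed, but it concerns a secondary objective only; the primary recurrence comparison and its sample size are untouched.

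**What to change.** Reconcile OBJECTIVES, SAFETY REPORTING, and the follow-up and discontinuation text in one of two ways.

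- **Keep the objective.** Amend SAFETY REPORTING so that all adverse events, as that section already defines them, are recorded in the CRF in every arm at the visits already scheduled in the first month, with expedited reporting kept for serious events. State whether haematocrit is measured after dosing in all arms; whether and when to measure it is for the investigators. The cost is a CRF page and some data entry.
- **Narrow the objective.** Limit it, and any safety conclusion, to serious adverse events and discontinuations, and make no claim about comparative tolerability or haemolysis. The cost is one sentence and the loss of that comparison.

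The first must be settled before enrolment, because uncollected data cannot be recovered later.

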Each participant has the right to withdraw from the study at any time. In addition, the investigator may withdraw a participant if he or she considers it necessary for any reason including:

- Significant non-compliance with study requirements
- An adverse event which requires discontinuation of the study medication or results in inability to continue to comply with study procedures
- Disease progression which requires discontinuation of the study medication or results in inability to continue to comply with study procedures
- Blood transfusion
- Development of severe malaria
- Loss to follow up

If an individual is prematurely discontinued from study treatment for any reason, the investigator will make every effort to perform the following evaluations: physical examination and vital signs assessment, haematocrit level, parasite count and AE assessment. The reason for withdrawal will be recorded in the CRF. If the subject is withdrawn due to an adverse event, the investigator will arrange for follow-up visits until the adverse event has resolved or stabilised.

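### The adverse event definition excludes malaria with no exception for serious outcomes, so a malaria death, malaria hospitalisation or progression to severe malaria carries no stated duty to report.

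*Protocol*

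**What the plan says.** The Safety Reporting section of the protocol limits safety work to observation, treatment and "recording and reporting only serious adverse events". Under Definitions, "an AE is either a drug-related side effect or a new or exacerbation of a pre-existing symptom, sign or illness (other than malaria"). The SAE definition that follows begins "A serious adverse event is an AE that" and lists the seriousness criteria, among them death, threat to life and hospitalisation.

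The reporting duty attaches to SAEs alone. "All SAEs will be reported by the site investigator to the Medical Monitor", within one day of awareness, and "The site investigator must also report the SAEs to the local ethics committee in accordance with local requirements".

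The section on discontinuation and withdrawal lists "Development of severe malaria" among the reasons for which the investigator may withdraw a participant, next to disease progression. For withdrawals, "The reason for withdrawal will be recorded in the CRF". If the withdrawal is due to an adverse event, "the investigator will arrange for follow-up visits until the adverse event has resolved or stabilised".

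Other sections bear on the point. Objectives makes the safety and tolerability of the regimens a secondary objective. The primary endpoint is recurrence of vivax malaria over 15 months. The sample size justification assumes relapse in 30% of the chloroquine-only arm and 4% of the 14-day primaquine arm.

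**The concern.** Keeping the study disease out of the adverse event definition is common and often sensible, above all when its return is the endpoint. It is safe only if the serious outcomes of that disease are reported some other way. Here the exclusion has no limit by severity, outcome, episode or malaria species, and the SAE definition inherits it.

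Two things are at stake. The first is oversight: the Medical Monitor and the ethics committee could go without prompt notice of the gravest malaria outcomes in the trial. The second is the safety comparison. The regimens are expected to differ in how often malaria returns, so a table of SAEs that omits serious malaria leaves out a harm that could differ between arms.

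**Working it through.** The protocol gives no figure on this point, so the check is a reading of the sections against each other.

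**Step 1. Is malaria outside the adverse event definition?** The definition has two limbs: a side effect of a drug, and a new or worsened symptom, sign or illness. The words in brackets take malaria out of the second limb. A malaria episode is not a drug side effect, so it does not enter by the first limb either.

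**Step 2. Does the exclusion carry over to serious events?** Yes. An SAE must first be an adverse event ("A serious adverse event is an AE that"). Death, threat to life and hospitalisation are tests applied to something already inside the definition. They do not admit an event on their own.

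**Step 3. Does any other reporting rule bring these events back?** I looked in each place where one might stand.

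| Section | What it does | Report to Medical Monitor or ethics committee? |
| --- | --- | --- |
| Safety Reporting, reporting procedures | Covers SAEs only | No, by steps 1 and 2 |
| Discontinuation/Withdrawal | Severe malaria is a discretionary withdrawal reason; the reason goes in the CRF | No onward report stated |
| Discontinuation/Withdrawal, evaluations | Examination, haematocrit, parasite count and an adverse event assessment | No; the assessment uses the same definition |
| Primary endpoint | Counts recurrence | No; severity, admission and death are not part of it |
| Patients with recurrent parasitaemia | Species, count, haematocrit, genotyping | No |
| List of abbreviations | Names a data and safety monitoring board | No section shown gives it a role |

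**Step 4. Does follow-up to resolution cover these participants?** That sentence applies when withdrawal is due to an adverse event. Severe malaria is not one by step 1, so a participant withdrawn for it falls outside the sentence, although severe malaria is a listed reason for withdrawal in the same section.

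**Step 5. Could the gap differ between arms, and by how much?** For malaria that returns, write the expected number of unreported events in an arm as N × r × s, where N is the number of patients, r the recurrence risk and s the share of recurrences with a serious outcome.

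- N = 50 and r = 0.30 or 0.04 (sample size justification): 50 × 0.30 = 15 recurrences on chloroquine alone and 50 × 0.04 = 2 on 14-day primaquine.
- After the 20% loss that the plan allows for, N = 50 × 0.80 = 40: 40 × 0.30 = 12 and 40 × 0.04 = 1.6.
- s is not given in the protocol, overall or by arm.

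The first two factors show a possible direction. Without s there is no count. Progression during the enrolment episode is a separate source of such events, and the documents give no rate for that either.

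**The case against.** **The brackets may be meant narrowly.** They could exclude only the malaria illness, so that a new sign or complication leading to admission or death would still count. That is a possible reading, but the protocol does not state it, and two sites could apply the definition differently. The ambiguity needs the same amendment.

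**The events are not lost.** This stands in part. Every recurrence counts towards the primary endpoint and is sampled, and the reason for a withdrawal is recorded. Serious malaria that leads to withdrawal can therefore be found later, by participant and so by arm. What is missing is a prompt safety report. The record also depends on a discretionary withdrawal, and a recurrence entry need not show its severity.

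**The follow-up sentence is a minimum.** It does not bar continued care, and the protocol provides treatment as needed elsewhere. That is fair. The point is only that the sentence as written does not reach a withdrawal reason listed just above it.

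**Readings that go further than the documents.** A reader might infer that serious primaquine haemolysis also escapes, because an unblinded investigator could attribute a fall in haematocrit to malaria. The documents do not support this: a drug-related effect sits in the first limb, which the malaria exclusion does not naturally govern, and attribution is a matter of judgement under any definition. A reader might also take the ratio of the two relapse rates as the imbalance in missing SAEs. That ratio is the planned contrast on the primary endpoint, which the trial counts in full, and says nothing about how often a recurrence is serious.

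**Conclusion.** The point holds as a gap in the reporting rule. On the literal wording, malaria death, malaria hospitalisation and progression to severe malaria create no duty to report to the Medical Monitor or the ethics committee, and no other section supplies one. This rests on reading the brackets as excluding malaria and its consequences. On the narrower reading the fault is an ambiguity with the same remedy.

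Its size cannot be stated. The assumed recurrence rates make an uneven omission plausible, but that serious malaria differs by regimen is an inference, and the protocol gives no rate of it. It would go too far to say that the SAE table will favour one arm, or that the events vanish from the trial record. The change is still worth making, because it concerns the gravest outcomes in the trial, bears on a stated objective and costs little.

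**What to change.** 1. In Safety Reporting, limit the exclusion to uncomplicated vivax malaria, that is, the enrolment episode and the recurrences counted as the endpoint.
2. In the same section, state that any malaria episode meeting one of the seriousness criteria already listed is an SAE, reported within the existing one-day limit and by the existing route. No new criterion is needed. A reader might want every blood transfusion made an SAE because it is a listed withdrawal reason, but that goes beyond the protocol's own criteria and is not part of this point.
3. Reconcile the withdrawal section with this, so that follow-up to resolution or stabilisation also covers participants withdrawn for such events.

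One drafting detail: the Safety Reporting section implies that some patients are in hospital, so the new sentence should say whether a planned stay for the enrolment episode counts as hospitalisation. Otherwise routine admissions could generate forms.

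The cost is two or three amended sentences and a few extra SAE forms, plus the occasional follow-up visit for a participant withdrawn for such an event. Treatment, allocation, endpoint and sample size are untouched.
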